### Recruitment {15}

To ensure adequate participant enrollment and achieve the target sample size, this trial will be conducted as a multicenter study involving five high-volume tertiary care hospitals in the Tokai region of Japan. Each participating center has extensive experience in endoscopic management of CBDS and a sufficient case volume to support enrollment. Regular investigator meetings will be held to monitor recruitment progress, identify enrollment barriers, and implement corrective measures as needed. Eligibility screening logs will document the number of patients screened, reasons for non-participation, and reasons for exclusion to improve transparency.

## Assignment of interventions: allocation

### Sequence generation {16a}

After patient enrollment, randomization will be performed using the UMIN INDICE cloud system. A computer-generated allocation sequence will assign participants in a 1:1 ratio to either the ESBD or EST groups. Stratified randomization will be applied based on two allocation factors: (1) presence or absence of pre-procedural biliary drainage, and (2) use or non-use of antithrombotic agents. Within each stratum, variable block sizes will be used to maintain allocation concealment. To ensure allocation concealment and reduce the predictability of the random sequence, details of any randomization restrictions will be maintained in a separate document inaccessible to investigators involved in participant enrollment or group assignment.

### Concealment mechanism {16b}

The allocation sequence will be implemented using the secure, centralized UMIN INDICE cloud-based randomization system. This system ensures allocation concealment by preventing investigators and study personnel from accessing the randomization sequence in advance. Participants will be randomized only after completing the eligibility confirmation and registration procedures, thereby maintaining strict concealment until assignment.

### Implementation {16c}

The computer-generated allocation sequence will be developed and managed by the UMIN INDICE system. Investigators at each participating center will be responsible for enrolling eligible participants. Once enrollment is completed, the system will automatically assign participants to either the ESBD or EST group according to the pre-programmed randomization algorithm.

## Assignment of interventions: blinding

### Who will be blinded {17a}

This is an open-label trial; therefore, neither participants nor treating endoscopists will be blinded to group allocation. Outcome assessors and data analysts will also not be blinded due to the nature of the intervention. However, to minimize bias in outcome evaluation, procedure-related adverse events will be classified and graded according to predefined criteria based on the American Society for Gastrointestinal Endoscopy lexicon, and all relevant outcomes will be objectively assessed using standardized metrics.

### Procedure for unblinding if needed {17b}

As this is an open-label trial, unblinding procedures are not applicable. All participants and treating physicians will be aware of the assigned interventions at the time of treatment.

## Data collection and management

### Plans for assessment and collection of outcomes {18a}

At each participating site, the principal investigator or co-investigators will collect baseline characteristics, procedural data, and outcomes from medical records and procedural findings. These data will be entered into the UMIN INDICE cloud system and stored as electronic case report forms. Each institution will prepare and maintain a separate linkage file that connects the study identification code with the individual participant, ensuring that personal identifiers are not used during data entry. All data queries or communications between the data management team or study office and the participating centers will be handled using only the study ID codes, in order to maintain confidentiality.

To ensure data quality, all investigators will receive instructions in advance regarding standardized definitions of each outcome and data entry procedures. Investigators will undergo training sessions and certification in data entry and outcome assessment procedures before trial initiation. Outcome assessment, including adverse event classification and severity grading, will follow predefined criteria based on the American Society for Gastrointestinal Endoscopy lexicon. The study does not involve patient-reported outcomes or questionnaire-based assessments.

### Plans to promote participant retention and complete follow-up {18b}

To ensure comprehensive follow-up and maximize participant retention, all patients will undergo clinical and laboratory evaluations on the day following the endoscopic procedure. Imaging studies such as computed tomography will be performed as clinically indicated.

Although no specific follow-up protocol is mandated during the post-treatment observation period, patients presenting with symptoms suggestive of adverse events will promptly undergo appropriate blood and imaging tests, following the same assessment principles used on the day after the procedure.

Long-term follow-up will continue until either the participant’s death or the end of the study’s follow-up period (i.e., 5 years after the final participant’s enrollment), whichever occurs first. Data collection during follow-up may include chart reviews, records from other institutions, or telephone interviews, as appropriate. Every effort will be made to obtain outcome data at the end of the study period whenever possible. A loss-to-follow-up rate of less than 10% will be targeted. To achieve this, we will maintain regular contact with participants through scheduled telephone calls and coordinate with referring hospitals for updated information. If the loss-to-follow-up rate approaches 10%, additional measures such as contacting family members or caregivers will be implemented.

### Data management {19}

All study data will be entered into the UMIN INDICE cloud-based data management system by investigators at each participating site. Data will be entered using anonymized study identification codes, and personal identifiers will not be included in the system to ensure confidentiality. Each site will securely maintain a linkage file to connect study IDs with individual participants. The data manager will also screen for missing or unplausible data and ask the corresponding investigator at each center for a data check using study ID codes only. Audit trails will be maintained to track all data modifications. Access to the data system will be restricted to authorized personnel with individual login credentials.

### Confidentiality {27}

All personal information will be handled in accordance with relevant privacy laws and institutional guidelines. Data handling will comply with the General Data Protection Regulation where applicable, in addition to local privacy laws. Participants will be assigned anonymized identification codes at the time of enrollment, and all study data will be managed using these codes. Personally identifiable information will not be included in study databases and will be securely stored at each site. Data sharing between institutions will be conducted using only anonymized codes to ensure confidentiality before, during, and after the trial.

### Plans for collection, laboratory evaluation, and storage of biological specimens for genetic or molecular analysis in this trial/future use {33}

This study does not involve the collection, storage, or laboratory evaluation of biological specimens for genetic or molecular analysis. No biospecimens will be collected for current or future research purposes.

## Statistical methods

### Statistical methods for primary and secondary outcomes {20a}

For the primary outcome, group comparisons of categorical variables will be performed using Pearson’s chi-square test or Fisher’s exact test, as appropriate. A two-sided *p*-value of less than 0.05 will be considered statistically significant.

For secondary outcomes, categorical variables will also be analyzed using Pearson’s chi-square test or Fisher’s exact test. Continuous variables will be compared using the *t*-test or the Mann–Whitney *U* test, depending on the distribution. Normality of continuous variables will be assessed using the Shapiro–Wilk test before applying the *t*-test. Time-to-event variables will be analyzed using the log-rank test, and survival curves will be constructed using Kaplan–Meier estimates. To examine factors associated with each event, multivariable analyses such as linear regression, logistic regression, and Cox proportional hazards models will be applied with covariate adjustment. For multiple subgroup analyses, Bonferroni correction will be applied to adjust the p-value threshold to control the family-wise error rate. If the proportion of missing data exceeds 10%, multiple imputation will be conducted as a sensitivity analysis in addition to the available-case analysis. A two-sided *p*-value < 0.05 will be considered statistically significant for all analyses. All analyses will be performed using R.

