### Sample size {14}

The sample size estimation was based on a two-sided chi-square test. A previous retrospective study comparing ESBD and EST reported that the incidence of procedure-related adverse events was 15.8% in the EST group and 4.4% in the ESBD group [3]. Based on these findings, a sample size calculation was performed using a two-sided test with a significance level (*α*) of 0.05 and a power of 80%, assuming a 1:1 allocation ratio. Accounting for an estimated 10% of ineligible or dropout cases, the final target sample size is set at 280 patients (140 in each group). In addition to the primary sample size estimation based on retrospective data, a sensitivity analysis will be performed using alternative event rates reported in other studies to ensure the robustness of the calculation.

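### The primary test leaves out the two randomisation stratification factors, which makes it slightly conservative and gives up a little power; a stratified test would recover this at no cost

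*Protocol article*

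**What the plan says.** Under Sequence generation {16a} the protocol article says: "Stratified randomization will be applied based on two allocation factors". The factors are presence or absence of pre-procedural biliary drainage and use or non-use of antithrombotic agents.

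Under Statistical methods for primary and secondary outcomes {20a} the primary analysis reads: "For the primary outcome, group comparisons of categorical variables will be performed using Pearson’s chi-square test or Fisher’s exact test, as appropriate". Neither stratification factor appears in it. The same section plans linear, logistic and Cox models with covariate adjustment, but their stated purpose is to look for factors associated with each event. They are not named as the primary comparison, and the two factors are not named as covariates. Antithrombotic use is listed as a subgroup variable in {20b}; drainage is not.

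Under Sample size {14} the design basis is given as: "The sample size estimation was based on a two-sided chi-square test".

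**The concern.** The trial balances the arms on two factors and then sets them aside in the confirmatory comparison. At least one is likely to matter for the primary endpoint. Bleeding is one of the two adverse events the protocol most expects, and the protocol excludes patients whose antithrombotic agents cannot be stopped or adjusted.

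Stratified allocation removes chance imbalance between the arms on these factors, so the difference in event proportions varies less than it would under simple randomisation. An unstratified test does not know this. Its variance still contains the between-stratum part that the design has removed. If the factors are prognostic, that variance is too large, the test rejects too seldom under the null, and some power is lost. If they are not prognostic, nothing is lost.

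A smaller matter sits beside this. The sentence names two tests and gives no rule for choosing between them, and it does not say whether the chi-square carries a continuity correction.

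**Working it through.** **1. The plan's own sample size.** Inputs from Sample size {14}: "procedure-related adverse events was 15.8% in the EST group and 4.4% in the ESBD group"; a "two-sided test with a significance level (*α*) of 0.05"; "a power of 80%, assuming a 1:1 allocation ratio"; and "Accounting for an estimated 10% of ineligible or dropout cases".

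With p1 = 0.158, p2 = 0.044, mean p = 0.101 and d = 0.114:

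- Without correction: n = [1.960·√(2·0.101·0.899) + 0.842·√(0.158·0.842 + 0.044·0.956)]² / 0.114² = 108.5, so 109 per arm. Then 109/0.9 = 121.1, so 122 per arm.
- With continuity correction: n′ = (n/4)·[1 + √(1 + 4/(n·d))]² = 125.4, so 126 per arm. Then 126/0.9 = 140 per arm, or 280 in total.

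The stated 280 is reproduced exactly by the continuity-corrected chi-square formula.

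**2. Why omitting the strata is conservative.** For stratum shares w_k and event rates p_k with overall rate p, p(1−p) = Σ w_k·p_k(1−p_k) + Σ w_k·(p_k−p)². The unstratified test uses the left side. Stratified allocation has removed the last term from the real variability. That term is zero only if the strata do not differ in risk.

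**3. Size of the effect.** The documents give neither the stratum shares nor the strength of the association, so these are assumptions: 280 patients, 30% on antithrombotics, 40% drained. Trials were simulated with allocation balanced within the four strata. The unstratified Pearson test was compared with the Cochran-Mantel-Haenszel (CMH) statistic without correction, [Σ(a_k − E_k)]² / Σ V_k. Here a_k is the number of events in one arm of stratum k, and E_k and V_k are its hypergeometric mean and variance.

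| Assumed odds ratios (antithrombotics, drainage) | Type I error, unstratified |
|---|---|
| 2 and 1.5 | 4.8% |
| 3 and 2 | 4.5% |
| 4 and 2.5 | 4.2% |

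A second simulation under the same settings gave 4.1% to 4.7%. CMH held about 4.9% to 5.0%.

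Power with odds ratios of 3 and 2:

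- At 15.8% vs 4.4%: 91.1% unstratified, 91.8% CMH.
- At 15.8% vs 7%: 65.1% unstratified, 66.8% CMH.

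Over the whole range in the table, the gain from CMH is about 0.3 to 1.1 points at the design rates and up to 2.7 points at 15.8% vs 7%.

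A wider check used stratum shares of 30/30/20/20% and the same odds ratio for both factors. Unstratified type I error was 4.9% at odds ratio 1 (no loss) and fell to 3.1% at odds ratio 10. The power loss there was about 2.5 points at the design rates. CMH stayed between 4.9% and 5.1% throughout.

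**4. The secondary ambiguity.** This was checked by exact enumeration of all 2×2 tables at 140 per arm:

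- Power at the design rates is 90.6% for Pearson and 87.2% for Fisher or the corrected chi-square.
- With 17 vs 7 events of 140, Pearson gives p = 0.033, Fisher p = 0.053 and the corrected chi-square p = 0.055.
- Pearson and Fisher fall on opposite sides of 0.05 in 3.5% of trials at the design rates, and in 8.8% at 10% vs 4%.
- Fisher never rejected where Pearson did not. Taking the smaller p-value every time therefore gives a maximum type I error of 5.04% (5.03% at 126 per arm) over event rates from 0.5% to 20%.
- Under the usual rule of switching to Fisher when an expected count is below 5, equal arms need fewer than 10 events in total. The design expects 140·0.158 + 140·0.044 = 28.3. The chance of fewer than 10 is about 0.00001 at the design rates and 0.5% at 10% vs 4%.

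**The case against.** The strongest reply is that an unadjusted test after stratified randomisation is a valid analysis that errs on the safe side, that its cost rests on assumed odds ratios, and that details such as a covariate list or a rule for choosing the test belong in the analysis plan mentioned under Interim analyses {21b}, which is not shown.

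Much of this stands. The cost is small and depends on prognostic strength that the documents do not give. The absence of a selection rule or a statement on continuity correction is no finding by itself. What does not fall away is the main point: the article does not leave the primary method open but states an unstratified one. An analysis plan with a stratified primary test would contradict that statement.

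Three stronger readings are tempting and are not supported:

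- **That the false-positive rate is compromised.** Omitting the strata moves the error rate below 5%. Free choice between Pearson and Fisher, even by the unblinded analysts described in {17a}, takes it no higher than about 5.04%.
- **That the plan as ordinarily read can yield opposite verdicts.** Tables with split results exist, but the customary expected-count rule would almost never select Fisher here, and {14} already names a chi-square test. The choice between corrected and uncorrected chi-square does remain unstated.
- **That the sample size is wrong because only the corrected formula reproduces it.** A corrected chi-square is still a chi-square. At 280 patients and the design rates, power is above 80% with either test.

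**Conclusion.** The point holds as a modest loss of efficiency, not as an error of validity. The stated primary comparison ignores both factors used to stratify randomisation. If those factors carry odds ratios of 2 to 4 and 1.5 to 2.5, with 30% on antithrombotics and 40% drained, the test runs at about 4.1% to 4.8% instead of 5%. It gives up about 0.3 to 1 point of power at 15.8% vs 4.4%, and up to about 2.7 points if the ESBD rate is nearer 7%. With weakly prognostic factors the loss is close to nil. There is no alpha inflation and, at the design rates, no shortfall against the planned 80%. The open wording on the test is secondary and matters only for borderline results.

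**What to change.** State one primary analysis in {20a}: a Cochran-Mantel-Haenszel test without continuity correction, stratified by pre-procedural biliary drainage and antithrombotic use as recorded at randomisation, reported with the stratum-adjusted risk difference and its 95% confidence interval. Keep the unstratified Pearson chi-square, uncorrected, as a supportive analysis, and drop the Fisher alternative for the primary outcome.

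The cost is a change of wording in the protocol and the analysis plan. Both factors are already recorded at randomisation, and the sample size need not change. Recruitment is scheduled to run to 31 March 2027 and no interim analysis is planned, so the change can be dated and recorded before any comparison of the arms.

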**Secondary endpoints**			
Type and severity of procedure-related AEs	Classified using ASGE lexicon; detailed criteria applied for bleeding and pancreatitis (see Notes)	Descriptive	Within 30 days from the procedure
Technical success rate	Completion of ESBD or EST according to protocol	Binary outcome	Day of procedure
Clinical success rate	Complete stone removal in a single session	Binary outcome	Day of procedure
Total procedure time	Time from cannulation to completion of stone removal	Continuous (minutes)	Day of procedure
Time required for stone removal	Time from end of ESBD or EST to completion of stone removal	Continuous (minutes)	Day of procedure
Proportion of cases requiring lithotripsy	Use of mechanical lithotripsy (excluding mechanical tools used without fragmentation), electrohydraulic lithotripsy, or laser lithotripsy	Incidence proportion	Day of procedure
Stone recurrence rate	Reappearance of bile duct stones post-removal	Incidence proportion	5-year follow-up
Time to stone recurrence	Days from successful stone removal to confirmed recurrence	Time-to-event	5-year follow-up
Biliary event rate	Any biliary event (e.g., stone recurrence, cholangitis, cholecystitis, liver abscess, biliary cancer)	Incidence proportion	5-year follow-up
Time to biliary event	Days from successful stone removal to occurrence of any biliary event	Time-to-event	5-year follow-up
**Notes on adverse event definitions** The definitions and severity grading of procedure-related adverse events will follow the ASGE lexicon [7]. Among these, bleeding and pancreatitis are the most anticipated adverse events in this study and represent key safety outcomes; therefore, more detailed criteria are specifically defined for these two events **-Bleeding:** *Intra-procedural bleeding*: requires hemostatic intervention (excluding preventive measures) *Post-procedural bleeding*: confirmed by endoscopy or imaging study such as computed tomography, or inferred from clinical findings such as hematemesis, melena, or a drop in hemoglobin level that cannot be explained by other causes **-Pancreatitis:** The diagnosis is established when at least two of the following three criteria are met: (1) acute abdominal pain and tenderness in the upper abdomen, (2) elevated levels of serum or urinary pancreatic enzymes, and (3) imaging findings indicative of acute pancreatitis [8]			

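### Kaplan-Meier curves for 5-year stone recurrence and biliary events would in effect censor deaths and so overstate the risk, and the 5-year proportions have no stated cut at 5 years per patient

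*Protocol article*

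**What the plan says.** Table 1 of the protocol article lists stone recurrence and biliary events twice each: as an incidence proportion and as a time-to-event outcome, all four at the 5-year follow-up. Recurrence is defined as "Reappearance of bile duct stones post-removal", and its time-to-event version as "Days from successful stone removal to confirmed recurrence". Death is a component of neither endpoint.

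The section on statistical methods {20a} assigns the methods. For the time-to-event versions: "Time-to-event variables will be analyzed using the log-rank test, and survival curves will be constructed using Kaplan–Meier estimates". Categorical secondary outcomes are compared by chi-square or Fisher's exact test. Cox models are named for factors associated with events. No competing-risk method appears.

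The section on retention and follow-up {18b} sets the observation window: "Long-term follow-up will continue until either the participant’s death or the end of the study’s follow-up period". That period ends on one calendar date for everyone, namely "5 years after the final participant’s enrollment". The trial status section gives recruitment from 21 April 2025 to 31 March 2027.

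**The concern.** A patient who has died cannot have a recurrence. Kaplan-Meier treats a censored patient as still at risk and as exchangeable with those still observed. If observation ends at death and death is not an event, deaths enter as censorings. One minus the curve then answers what the risk would be if nobody died, which is higher than the proportion of patients who actually have a recurrence within 5 years.

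The second issue is the label on the proportions. Potential follow-up differs between early and late enrollees, so a proportion that counts every recorded event mixes horizons from 5 to almost 7 years.

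The absolute 5-year risks are at stake. The Discussion expects the long-term results to inform practice guidelines. Deaths are unlikely to be negligible: there is no upper age limit, and the planned subgroups include performance status, liver cirrhosis and renal failure.

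**Working it through.** **No planned figure to reproduce.** The protocol states no expected recurrence rate, death rate or power for the 5-year endpoints. Its target of 140 per arm is derived from 30-day adverse events and does not bear on this point. All rates below are assumptions.

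**Follow-up range.** From 21 April 2025 to 31 March 2027 is 709 days, and 709 / 365.25 = 1.94 years. Potential follow-up from enrolment is therefore 5.0 years for the last patient and 5 + 1.94 = 6.94 years for the first. The event clock starts at stone removal, up to 14 days after enrolment, which makes no material difference.

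**Model.** Constant yearly hazards, r for recurrence and d for death:

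- Kaplan-Meier with deaths censored: KM = 1 − exp(−5r)
- Actual 5-year risk (cumulative incidence): CI = r/(r+d) × [1 − exp(−5(r+d))]
- Proportion counting all events to the closing date: the mean of the cumulative incidence over follow-up times spread evenly from 5 to 6.94 years

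**Central example, r = 3% and d = 5% per year.**

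- KM = 1 − exp(−0.15) = 13.93%
- CI = 0.03/0.08 × [1 − exp(−0.40)] = 0.375 × 0.3297 = 12.36%
- Overstatement = 1.57 points, and 13.93/12.36 = 1.127, so about 13% relative
- Proportion to the closing date = 14.2%, which is 1.9 points above the 5-year risk

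**Range of assumptions.**

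| r per year | d per year | KM | 5-year CI | KM excess (points) | KM excess (relative) | Proportion to closing date |
|---|---|---|---|---|---|---|
| 2% | 3% | 9.5% | 8.8% | 0.7 | 8% | 10.3% |
| 2% | 8% | 9.5% | 7.9% | 1.7 | 21% | 9.0% |
| 3% | 5% | 13.9% | 12.4% | 1.6 | 13% | 14.2% |
| 4% | 3% | 18.1% | 16.9% | 1.3 | 7% | 19.5% |
| 4% | 8% | 18.1% | 15.0% | 3.1 | 21% | 17.0% |

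Excesses are computed before rounding. The relative error depends almost entirely on mortality. With a 15% Kaplan-Meier risk, 5-year mortality of 5%, 20% and 40% gives factors of 1.03, 1.11 and 1.27.

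**A proportion that is cut at 5 years.** With deaths kept in the denominator and nobody lost, it equals the cumulative incidence. Loss moves it modestly. With a 15% Kaplan-Meier risk, 20% five-year mortality and 10% loss, the true value is 13.5%. The proportion reads 12.8% if lost patients count as event-free and 14.0% if they are excluded.

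**Log-rank test.** In 4,000 simulated trials with 140 per arm and no difference in recurrence hazard, the test rejected in 5.5% at 20% mortality in both arms, 5.0% at 30% in both, and 5.0% at 30% versus 20%. It keeps its size because it tests the cause-specific hazard. In the unequal-mortality case the actual 5-year risks differed by 0.8 points on average, while the Kaplan-Meier difference was near zero.

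**The case against.** **The SAP may settle this.** The interim analyses section says short- and long-term outcomes follow a predefined statistical analysis plan, which is not shown. Handling of death and the analysis cut-off often sit there. This carries weight for the 5-year cut, which is a request for clarification. It carries less for the curves, because the protocol names the estimator itself.

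**Censoring of deaths is not stated.** That is correct. It is inferred from three provisions: Kaplan-Meier, follow-up ending at death, and endpoints that exclude death. No other ordinary reading fits all three.

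**The size is assumed and may be small.** Also correct. In the central example the 1.6-point excess is smaller than the sampling error of one arm, √(0.124 × 0.876 / 140) = 2.8 points. But the bias has a known direction, does not shrink with sample size and is avoidable. With similar mortality in both arms, both curves are raised to a similar degree.

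**Stronger readings that a reader might infer, and that the documents do not support:**

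- *That neither long-term figure can estimate a 5-year risk.* Everyone has at least 5 years of potential follow-up from enrolment, so a proportion cut at the tabled time point does so, apart from losses. Nothing says that events up to 6.9 years will be counted.
- *That the proportion errs by counting patients who died as recurrence-free.* Cumulative incidence also keeps them in the denominator without an event, which is right for actual risk.
- *That lost patients will count as event-free.* The section on missing data {20c} makes available-case analysis primary, and {20a} adds multiple imputation as a sensitivity analysis above 10% missing.
- *That the log-rank test is invalid.* It is a valid comparison of cause-specific hazards.

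**Conclusion.** The point holds in a limited form. As written, the plan leads to Kaplan-Meier curves that censor deaths, and one minus these curves overstates the 5-year risk of recurrence and of biliary events. The overstatement is about 0.7 to 3.1 points (7 to 21% relative) if recurrence runs at 2 to 4% and death at 3 to 8% per year. These are assumed constant hazards, not figures from the protocol. At 5% five-year mortality the relative overstatement would be only about 3%.

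The 5-year proportions are ambiguous rather than wrong. They are sound if cut at 5 years per patient, apart from losses, and too high if every event to the closing date is counted (by 1.9 points in the central example). Only secondary endpoints are affected. The 30-day primary comparison and the planned log-rank and Cox comparisons stand.

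**What to change.** For stone recurrence and biliary events:

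1. State that death without the event is a competing event.
2. Replace the Kaplan-Meier risk curves with Aalen-Johansen cumulative incidence curves. Report the value at exactly 5 years per arm and the difference between arms with a 95% CI.
3. Use that same estimate in place of the crude incidence proportion and its chi-square test. It cuts at 5 years per patient and allows for loss to follow-up by censoring lost patients when last known event-free.
4. Keep log-rank and Cox, labelled as comparisons of the cause-specific hazard. Gray's test may be added but is optional.

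If the SAP already says this, the protocol's methods section and Table 1 need only be aligned with it. The cost is a few lines of text and minor extra analysis in R, the software already planned. No new data are needed, since death ends follow-up and its date should therefore already be recorded.
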